### Platelet rich plasma and adipose derived Mesenchymal stem cells in knee OA treatment- overview

Nowadays, PRP is commonly used in medicine to enhance expression of growth factors and cell rebuilding process not only in orthopedics but dermatology and dentistry as well [30, 31]. In OA treatment PRP is thought to have an influence on the whole joint environment by increasing chondrocyte proliferation [32], reduction of the inflammatory process [33, 34] and enhancing the secretion of hyaluronic acid (HA) as well [35]. It is well established that PRP is more effective in knee OA treatment than placebo (saline intra-articular injections) [12, 36–39]. More discrepancies among researchers exist when it comes to comparing the effectiveness of PRP and HA treatment. Some authors have found no differences between the groups treated with PRP and HA [34, 36], others [40–42] prove PRP injections alone or in combination with HA to be more effective than HA injections alone.

The autologous fat tissue, which contains numbers of pericytes [37, 38], serves as a kind of drugstore after the injection into the affected joint. It is thought that they secrete bioactive molecules and stimulate other type of cells by cell- cell contact [37]. The effects of autologous fat tissue activity are apoptosis inhibition, enhancement of angiogenesis and stabilization of the new vessels, stimulation of the progenitors to appropriate differentiation [37, 39]. Some authors combine intra-articular injections of autologous fat tissue with arthroscopic debridement [15, 43, 44] or microfractures [45–47], but autologous fat tissue alone may also improve degenerated joint condition [42, 48–51].

## Discussion

This study protocol has several strengths and weaknesses. Undoubtedly one of strongest point of this study is wide, multidimensional functional assessment, which will give a large amount of objective data. To our knowledge, this research is the first one which includes the battery of functional tests and MVIC as an outcome measurement tool. This study will use 4 questionnaires, including WOMAC, which is described by physicians as a gold standard for assessing the effectiveness of knee OA treatment [45, 52].

On the other hand this study has several limitations. Primarily - the lack of blinding and we consider this as a risk of both, subject and investigator bias. Next and equally important limitation is a small size of the study. Furthermore, autologous fat tissue procedure is definitely more invasive and more stressful for the patients than PRP procedure. Hence, taking all into consideration, to adopt autologous fat tissue as a knee OA therapy, based on the future results, we have to detect definite, statistically significant and clinically noticeable difference.

Our PRP procedure gives us the possibility to examine the patient and assess the reaction to intra- articular injection 3 times (3 injections) in 7 day interval. These visits are often associated with physical therapy, which consists of manual therapy and individualized exercise program. Autologous fat tissue procedure does not give us such a possibility. The doctor and physiotherapist see the patient on the day of the surgery and 2 weeks after, during a control visit, which is also associated with physical therapy. Thus, there are some discrepancies between the two procedures at the beginning of the treatment process.

It has been proven that intra- articular injection of autologous fat tissue or PRP is a safety treatment option of knee OA [46, 47]. The most common complications after the intra- articular injection are pain and swelling of treated knee, but this improve after cold compression and NSAIDs. Also there were no cancer incidents reported after autologous fat tissue or PRP implantation [47].

Subject recruitment has started after we received Bioethical Committee approval.

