### Inclusion and exclusion criteria

All activities related with the study will be performed at the Department of Spine Disorders and Pediatric Orthopedic Surgery, Poznan University of Medical Sciences and Rehasport Clinic in Poznan, Poland. These include patient identification, explanation of all procedures, treatment and functional assessment. The same inclusion criteria have been established for an Experimental Group (subjects treated with autologous fat tissue) and a Control Group (subjects treated with PRP). Those criteria consist of: symptomatic knee OA, age between 45 and 65 y.o., Kellgren- Lawrence grades I – III OA, no or minimal positive effects of previous conservative treatment (rehabilitation, hyaluronic acid injections, steroid injections), VAS pain level minimum 4 in one knee, VAS pain < 2 in the contralateral knee. Those patients who meet inclusion criteria will be allocated to Fat Tissue Group or PRP Group randomly (Fig. 1). The exclusion criteria were as follows: use of local corticosteroids up to 3 months or hyaluronic acid injections up to 6 months prior to the study, past or present joint infection, previous knee arthroscopy surgery up to 1 year prior to examination, peripheral inflammatory diseases (rheumatoid arthritis, spondyloarthropathies, etc.), total arthroplasty and osteotomy, ankylosis of the joint, dermatitis or dermatological disease at the intended injection site, coexistence of degenerative changes in other limb joints (hip, foot), cancer, oral corticosteroid therapy, use of medicines that affect blood clotting, pregnancy or breast-feeding. Before randomization, patients will sign a suitable consent form. All participants will be obliged not to use any anti-inflammatory drugs for the entire duration of the study. Moreover, every volunteer will receive a brochure approved by Research and Development Department which contains all of the information regarding protocol (procedures, outcomes assessments, schedule of visits, researchers team, possible complications). Draw is made at the Doctor’s room after subject’s qualification and the participant choose the number of the group 1 or 2, Fat Tissue Treatment or PRP treatment, respectively. At the stage of treatment there is no possibility for patients to be blinded because the procedure requires adipose tissue harvesting. However, during all other stages, the procedure will be blinded, in a database each participant will have a special code to minimize the risk of identification as well as reporter biases.

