### PRP procedure

PRP preparation takes place in an outpatient clinic. The whole process, from blood collection to PRP injection, takes approximately 10 min. It takes places in the treatment room at room temperature and day light exposure. No commercial kit are used. 10-ml sterile collecting tubes containing citrate will be placed in a centrifuge (Centrifuge MPW- 223e) with a tilting rotor. Rotation will last 7 min at 2320 * g. After centrifugation, PRP will be collected up to 3 ml for separate 10-ml syringe. 3 ml of PRP will be injected into the knee joint. Procedure will be repeated three times in 7 day interval.

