### Injection procedure

Joint injection will be performed by TP or PB in the same manner for both groups: patient placed in supine position, affected knee extended, a 21-Gauge needle inserted into the suprapatellar pouch, in case of joint effusion – aspiration of synovial fluid and finally administration of autologous fat tissue or PRP.

For the first 2 weeks after injections patients will be asked to limit their activity. 2 weeks after the third injection, normal activity will be allowed. Patients will be instructed to perform physical exercises, including cycling, swimming and full-body exercises. No physical therapy will be recommended.

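### Physical therapy is said not to be recommended, yet the Discussion attaches it to three PRP visits and one fat tissue visit, so unequal early co-treatment is mixed into the comparison

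*Protocol article*

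**What the plan says.** Two procedure sections carry the same sentence: "No physical therapy will be recommended". It closes Lipoaspiration procedure, which concerns the fat tissue arm, and it closes Injection procedure, which covers both groups. In each place it follows general advice to cycle, swim and exercise.

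PRP procedure sets the number of PRP visits: "Procedure will be repeated three times in 7 day interval". The Discussion describes what happens at them: "These visits are often associated with physical therapy, which consists of manual therapy and individualized exercise program". For the fat tissue arm the Discussion says: "The doctor and physiotherapist see the patient on the day of the surgery and 2 weeks after, during a control visit", and adds of that visit: "which is also associated with physical therapy". The authors then concede: "Thus, there are some discrepancies between the two procedures at the beginning of the treatment process".

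The section on ethics, data management and statistical analysis makes the comparison of the arms at every time point the main purpose. It names BMI, age, sex and OA grade as the possible confounders considered at the start.

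On drugs, Inclusion and exclusion criteria says: "All participants will be obliged not to use any anti-inflammatory drugs for the entire duration of the study". The Discussion says of pain and swelling after injection: "but this improve after cold compression and NSAIDs".

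**The concern.** A clinic that does not recommend physical therapy, yet often attaches it to its own treatment visits, has given two accounts of the same thing, and the article does not say which one governs. The second account also differs by arm, because the PRP schedule brings patients back more often.

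The article itself treats this co-treatment as active. Its Background puts aerobic and strength training among first-line recommendations for knee OA and lists manual therapy among the options for symptom relief. The outcomes are pain and function questionnaires, three functional tests and knee strength, which are the things such therapy is meant to change.

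Randomization does not remove the problem. The imbalance arises after allocation, from the visit schedule of each arm, and patients and treating staff know the arm. If therapy helps, part of any PRP improvement comes from it and the advantage of fat tissue is understated. A null result would then be hard to read as absence of benefit from the fat tissue procedure, and a larger sample would not cure this.

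**Working it through.** The article gives no sample size, effect size, SD or therapy uptake, so there is no stated figure to reproduce. The check sets the sections side by side and counts contacts.

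**Step 1: the rule against the practice.**

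| | Fat tissue | PRP |
|---|---|---|
| Procedure sections | therapy not recommended (Lipoaspiration procedure; Injection procedure) | therapy not recommended (Injection procedure) |
| Discussion | therapy associated with the 2-week control visit | therapy often associated with the injection visits |

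Both arms show the mismatch.

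**Step 2: early occasions for therapy.**
- PRP: 3 injection visits at 7-day intervals, so up to 3 occasions. The word used is *often*, so 3 is a ceiling.
- Fat tissue: 2 early contacts (day of surgery and 2 weeks), of which 1 is said to involve therapy.
- Difference: up to 3 − 1 = 2 occasions. If the day of surgery were also counted, up to 3 − 2 = 1.

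**Step 3: timing.** Three visits 7 days apart span 2 × 7 = 14 days, and the fat tissue control visit is at 2 weeks. All of these contacts precede the 1-month assessment. Any effect should be most visible at 1 and 3 months; the documents do not show whether it would last to 6 or 12 months.

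**Step 4: cover in the analysis.** The four named factors are all fixed at baseline. None captures a treatment received after allocation.

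**Step 5: possible size, on assumptions only.** A rough formula is: shift = (difference in uptake between arms) × (effect of therapy in SD). Neither input is in the documents. Assuming an uptake difference of 25 to 75 percentage points and an effect of 0.2 to 0.5 SD:
- low end: 0.25 × 0.2 = 0.05 SD
- high end: 0.75 × 0.5 = 0.375, about 0.38 SD

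The range runs from negligible to material. It shows only that the article does not allow the size to be judged. The direction, if therapy helps, is toward PRP.

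**The case against.** Several counter-arguments have force.

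- **Not recommended is not forbidden.** The sentence follows the advice on exercise after the restricted period, while the Discussion describes contacts at the start. Supervised contact early and no referral later would be compatible. That stands as a possible reading, but the article does not state it, and it would leave the early imbalance in place.
- **The authors disclose the discrepancy.** True, but disclosure neither reconciles the sections nor says how the results will be read.
- **The confounder list is open.** The analysis section plans repeated checks for confounders and presents its list as a starting point. Therapy could be added, but nothing in the article names it.
- **The effect may be small.** Eligible patients had little or no benefit from earlier conservative treatment, including rehabilitation. This may limit the effect without removing it. The bias also runs against a false claim for fat tissue.

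Stronger readings are tempting, and the documents do not support them:

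- A reader might infer unequal NSAID use. The NSAID sentence is a general remark on complications, beside statements that cite earlier work. It does not say that participants will take these drugs. It concerns the injection, which both arms receive and the PRP arm receives three times, so no direction can be inferred.
- A reader might infer that therapy goes unrecorded, since Table 1 has no row for it. That table also omits the second and third PRP injections and the 2-week visit, so it is not exhaustive, and a condensed article may leave such records to the full protocol or case report form.
- A reader might take the Discussion to say that fat tissue patients have no access to therapy. The possibility it says they lack is most naturally repeated examination, and the text goes on to mention therapy at their control visit.
- A reader might say that the result could otherwise be credited to the injected product alone. The stated aim is to compare two methods, which already differ in anaesthesia, liposuction, number of injections and weight bearing.

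**Conclusion.** The point holds for physical therapy. The procedure sections and the Discussion disagree, and the Discussion gives the PRP arm more occasions: up to three, against one in the fat tissue arm. As written, unequal early co-treatment is part of the between-arm difference, most plausibly at 1 and 3 months. If therapy helps, it favours PRP. The conclusion rests on reading the Discussion as describing trial patients, which its wording about the authors' own PRP procedure supports. The size is unknown, and the SD range above depends wholly on assumed inputs.

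The anti-inflammatory statements call for one clarifying line and carry no finding of bias.

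**What to change.** 1. Reconcile Lipoaspiration procedure and Injection procedure with the Discussion, so that one statement on physical therapy governs both arms. What the rule should be is for the investigators.
2. Record the number of physical therapy sessions per patient in both arms, if the full protocol does not already require it, and report it by arm. The count should cover the PRP injection visits and the 2-week control visit, which lie outside Table 1. Reporting is preferable to adjusting the main comparison for sessions, because they are received after allocation and follow from the arm.
3. If contacts remain unequal, say in the conclusion that the trial compares two treatment packages, each including its visits and therapy.
4. As a secondary clarification, state how the ban on anti-inflammatory drugs relates to the general NSAID remark in the Discussion.

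The cost is a change of wording and a minor addition to the visit forms.

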## Data Availability

The datasets used during the current study are available from the corresponding author on reasonable request.

## Abbreviations

OA: Knee osteoarthritis
MSCs: Mesenchymal stem cells
PRP: Platelet rich plasma
EULAR: European league against rheumatism
NICE: National institute for health and clinical excellence
NSAIDs: Non-steroidal anti-inflammatory drugs
BMSCs: Bone-marrow derived stem cells
PROMs: Patient reported outcome measures
KOOS: The knee injury and osteoarthritis outcome score
IKDC 2000: International knee documentation commitee 2000
WOMAC: Western ontario and mcmaster universities osteoarthritis index
EQ- 5D- 5 L: Health questionnaire
TUG: The timed up and go test
5xSTS: The 5 times sit to stand test
10mWT: The 10 m walk test
MVIC: Maximal voluntary isometric contraction
HA: Hyaluronic acid
